### Data management and monitoring

Electronic case report forms (CRFs) for the PIROUETTE-PTA trial are developed on the infrastructure of the Clinical Study Information System (CSIS) in cooperation between the coordinating investigator and a data manager at the Clinical Research Center of National Cheng Kung University Hospital. CSIS is the information management service provided by the Taiwan Clinical Trial Bioinformatics and Statistical Center, Training Center, and Pharmacogenomics Laboratory to facilitate the coordinating investigator in building up the electronic CRF system in investigator-initiated trials. This resource center is funded by the National Research Program for Biopharmaceuticals under grant support by the Ministry of Science and Technology (grant number 104-2325-B-002-033) and the Center for Systems and Synthetic Biology in National Yang-Ming University in Taiwan. Access to the CSIS will be possible around the clock every day and data can be entered continuously for all the randomly assigned patients. The coordinating investigator will have access to monitor the data input. If the entry is partially or completely missing or seems flawed on one or more randomly assigned patients, the coordinator will have the opportunity to contact the primary investigator in order to correct or complement data inputs to optimize the quality of the data. There are 13 CRFs to be filled on the CSIS at each indicated visit in the current study; Additional file 3 shows clinical data to be collected and recorded in more detail. The steering committee has access to the full trial dataset.

Original CRFs and source document will be kept on file and stored in numerical order and in a secure place with limited access at the participating site. All study-related records, materials, or documents are identified only by a coded identification number to keep participants’ confidentiality, whereas any records that should contain names or other personal identifiers, such as informed consent forms, will be stored separately from study records. An inspection team will select participating sites to monitor quality of the study at audit visits. Besides, a subset of the original CRFs will be requested for quality control during study. When a form is selected, the participating site staff will send the copy to the data management committee for inspection and double data entry.

We will provide a data and safety monitoring plan rather than establishing a data and safety monitoring committee because local IRBs consider that the interventions performed in the current study are medical routines. The data and safety monitoring plan includes reporting SAEs on time, increasing monitoring frequency, and analyzing safety data every 3 months. An interim analysis is performed on the primary endpoint by an independent statistician, who is blinded for the treatment allocation, when 50 % of patients have been randomly assigned and have completed 6-month follow-up. The statistician will report to the steering committee. The steering committee makes the final decision to terminate the trial and will report to the IRB of National Cheng Kung University Hospital. The trial will be ended by using symmetric stopping boundaries at a *P* value of less than 0.001. The trial will not be stopped in case of futility unless the statistician advises otherwise and the steering committee decides to terminate the trial for futility after discussion.

An adverse event that meets the criteria for an SAE between study enrollment and the end of the study will be reported to the local IRB. An SAE for this study is any untoward medical occurrence causing any of the following: a life-threatening condition, severe or permanent disability, or prolonged hospitalization. An SAE occurring after a participant withdraws consent from the study will not be reported unless the investigators consider that the event might have been caused by the protocol procedure. We will continue health care for trial participants regardless of having potential trial-related harm.

### Strategies to avoid and treat missing data

We have four strategies for limiting missing data in the conduct of this trial [28]: (1) selecting experienced investigators who have a good track record with respect to conducting clinical trials; (2) providing monetary incentives, which meet rigorous ethical requirement, to investigators and study staff for completeness of data collection; (3) providing reminder cards conveying the information that keeping participants in the trial until the end is important to investigators, study staff, and participants; and (4) keeping contact with participants. Missing data will be treated with the multiple imputation method.

### Power estimation and sample size calculation

As previously reported, the CARP (Coronary Artery Revascularization Prophylaxis) trial [13] shows a mortality of 23 % in the no-revascularization group, at a median of 2.7 years after randomization, and an incidence of MACE can be observed in 20 % of cases within 30 days after major vascular surgery. In addition, our previous study shows 25 % mortality, 8 % non-fatal myocardial infarction, 2 % non-fatal stroke, and 15 % coronary revascularization at a median of 10 months after PTA (total MACE rate is 35 %) [18]. Furthermore, a previous study showed that an absolute risk reduction of 16.7 % in MACE was observed in patients receiving routine coronary angiography versus selective group before major vascular surgery [6]. Therefore, we calculated that we would detect an absolute risk reduction of 16 % (estimated risk reduced from 40 % to 24 %) in primary composite events at long-term follow-up by enrolling a total sample of 450 patients (sample size of at least 432 with an estimated dropout rate of 4 %), with a one-sided alpha of 0.05, a power of 80 %, and a superior margin of 5 %. Although the superior margin is not absolutely necessary to demonstrate that the routine strategy is superior to the selective strategy, 5 % superior margin is to conservatively assess whether using the routine strategy would significantly reduce not only more but also at least 5 % greater in MACE than the selective strategy. The sample size would be smaller if there were no setup of the superior margin. Strategies for achieving adequate participant enrollment to reach the target sample size include selecting high-volume centers and interventionists for PTA and providing monetary incentives, which meet rigorous ethical requirements, to investigators and study staff for enrollment of participants.

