### Statistical analysis plan

To compare baseline characteristics between routine and selective strategy groups as well as the routine strategy group and the registration group, all interval-scaled variables will be presented as mean ± standard deviation. Skewed interval-scaled data will be reported as median (interquartile range). Categorical variables will be presented as frequency and proportion (percentage). Chi-squared or Fisher’s exact test will be used for comparison of categorical variables between groups, whereas Mann-Whitney *U* test or unpaired Student’s *t* test will be used for interval-scaled variables as appropriate.

To compare the endpoints between routine and selective strategy groups, each analysis will be performed by “intention-to-treat” and “per protocol”. Proportional or Fisher’s exact test will be used for analysis of the proportion of primary, secondary, and other endpoints between routine and selective strategy groups as appropriate. For primary endpoint, significantly greater than 5 % reduction of MACE in the routine strategy group compared with the selective strategy group will be analyzed. By using the same statistical methods, subgroup analysis will include comparison of the proportion of endpoints in subgroups of these two randomized arms, such as patients with critical limb ischemia (Rutherford classification of at least 4), chronic kidney disease (at least stage 3), end-stage renal disease, old age, different genders, tobacco smoking, diabetes mellitus, hypertension, hyperlipidemia, metabolic syndrome, anemia, bedridden, hypoalbuminemia, elevated high-sensitivity C-reactive protein level, and so on. Kaplan-Meier analysis will be used to study patient survival and event-free status by using the log-rank test (Cox-Mantel) to ascertain differences between groups. If more than one endpoint occurs within the follow-up period for assessing event-free status, only the first event will be used in the analysis. Generalized estimating equation will be used to address whether and how the clustering by centers. Missing data will be treated with the multiple imputation method.

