Although the main purpose of this study is not to compare the endpoints between the routine strategy group and the registration group or between randomized groups and the registration group, similar analyses as above will be performed to explore differences among patients in these groups. For all analyses, a *P* value of less than 0.05 is regarded as statistically significant. All statistical analyses are performed by using IBM SPSS Statistics 22.0 for Windows (IBM Corporation, Armonk, NY, USA), but the subgroup analysis is performed by using SAS software (Version 9.1.3; SAS Institute Inc., Cary, NC, USA).

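### The 80% power belongs to a one-sided 0.05 test against a 5-point margin, but the analysis section also names a test that cannot address the margin, omits sidedness, and gives no status to superiority without the margin.

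*Protocol article*

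**What the plan says.** All of this is in the protocol article, Methods/Design.

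- *Power estimation and sample size calculation*: the target effect is an "absolute risk reduction of 16 % (estimated risk reduced from 40 % to 24" percent), "with a one-sided alpha of 0.05, a power of 80 %, and a superior margin of 5" percentage points. At least 432 patients are needed, or 450 with 4% dropout. The next sentence concedes that the margin is optional: "Although the superior margin is not absolutely necessary to demonstrate that the routine strategy is superior to the selective strategy". It adds that the margin is a conservative choice and that the sample would be smaller without it.
- *Statistical analysis plan*, tests: a proportional test or Fisher's exact test, as appropriate, is named for the primary, secondary and other endpoints together. For the primary endpoint, a significant MACE reduction of more than 5% is then specified: "reduction of MACE in the routine strategy group compared with the selective strategy group will be analyzed". Kaplan-Meier curves with a log-rank test are listed for survival and event-free status.
- *Statistical analysis plan*, significance: for all analyses, a P "value of less than 0.05 is regarded as statistically significant". No sidedness is given.
- *Data management and monitoring*: one interim analysis of the primary endpoint, with "symmetric stopping boundaries" at P below 0.001. The null hypothesis it refers to is not given.

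**The concern.** The power statement is tied to one exact test: null hypothesis of a reduction of at most 5 points, one-sided 0.05. The analysis section repeats the margin but not the sidedness, and one of the two tests it offers for the primary endpoint answers a different question (any difference from zero). The two questions have different thresholds and different power.

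A result can therefore clear zero and miss 5 points. The article itself says that superiority needs no margin, yet it does not say what is concluded in that case. If this is left open, the choice between a positive and a negative report could be made after the result is known. A reader also cannot tell whether the 80% applies to the test that will be run.

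**Working it through.** **Inputs** (all from the power section; 1:1 allocation from the abstract): selective 0.40, routine 0.24, difference 0.16, margin 0.05, one-sided alpha 0.05, power 0.80, dropout 4%. The 5% margin is taken as absolute percentage points.

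**1. Reproduce the plan's figure** (unpooled variance)

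Variance sum = 0.40×0.60 + 0.24×0.76 = 0.2400 + 0.1824 = 0.4224.
n per arm = (1.645 + 0.842)² × 0.4224 / (0.16 − 0.05)² = 215.8, so 216 per arm and 432 in total. 432 / 0.96 = 450. Both figures match exactly, which also supports reading the margin as absolute points. A pooled variance would give 446 and a continuity correction 468.

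**2. Power of the readings the text allows, at 216 per arm**

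SE = √(0.4224/216) = 0.0442. Power = Φ((0.16 − m)/SE − z).

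| Test | m | z | Power |
|---|---|---|---|
| Margin, one-sided 0.05 | 0.05 | 1.645 | 80.0% |
| Margin, two-sided 0.05 | 0.05 | 1.960 | 70.1% |
| Zero difference, two-sided 0.05 | 0 | 1.960 | 95.1% (94.8% with pooled null variance) |
| Zero difference, one-sided 0.05 | 0 | 1.645 | 97.6% (97.4% pooled) |

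For 80% power on the margin at two-sided 0.05: (1.960 + 0.842)² × 0.4224 / 0.11² = 274 per arm, 548 evaluable, 571 with dropout.

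**3. Where the two questions part**

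Fix the observed selective rate at 0.40 and let d be the observed reduction. Solve d − m = z × √{[0.24 + (0.40 − d)(0.60 + d)]/216}:

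- zero difference, two-sided 0.05: d = 0.090
- margin, one-sided 0.05: d = 0.124
- margin, two-sided 0.05: d = 0.138

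Observed reductions between about 9.0 and 12.4 points exclude zero (two-sided) but do not establish more than 5 points (one-sided). If the planning variance is held fixed instead, the limits are 1.960 × 0.0442 = 8.7 and 5 + 1.645 × 4.42 = 12.3 points.

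**4. An example inside the window**

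86/216 against 62/216 is a reduction of 11.1 points. Against zero: two-sided P = 0.015 (Fisher 0.020). Against 5 points: SE = 0.0454, z = (0.1111 − 0.05)/0.0454 = 1.35, one-sided P = 0.089.

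**5. How often this would occur**

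The hypotheses are nested, so the chance of a split is the power against zero (two-sided) minus the power against the margin (one-sided). At the planned 16 points it is 95.1% − 80.0% = about 15%. At a true 12 points (40% to 28%, SE 0.0452) it is 76% − 46% = about 30%.

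**The case against.** A reader might infer that the analysis tests only zero difference, and that the trial could return two opposite primary answers. The article does not support this.

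- The analysis section restates the 5% criterion for the primary endpoint, and a proportional test can be run against a margin.
- Fisher's test is offered only as appropriate. With about 86 and 52 events expected (216×0.40 and 216×0.24), small counts give no reason to use it.
- The log-rank test is listed for survival and event-free status, not as the primary test.
- The hypotheses are nested: a reduction shown to exceed 5 points also exceeds zero. The split in the working is superior, but not shown superior by 5 points. That is a coherent result, and the margin was set knowingly to be conservative.

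A reader might also take the symmetric interim boundary as proof that the final test is two-sided. Stopping in either direction at P below 0.001 does not set the sidedness of the final test. The one-sided 0.05 is declared openly, so its 5% error rate for a benefit claim is a disclosed choice, not a contradiction.

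These points stand, and they narrow the concern. They do not explain why a test that cannot address the margin is named for the primary endpoint, which sidedness P below 0.05 carries, or what is concluded between the two thresholds. A fuller SAP could settle the exact statistic, but the article already fixes these elements, and they do not fit together.

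**Conclusion.** The sample size is correct for the test it assumes, and the margin does reach the primary analysis. What is not fixed is the decision rule: Fisher's exact test beside a margin criterion, P below 0.05 without sidedness, an interim P below 0.001 without a null, and no formal place for ordinary superiority.

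The 80% holds only for the one-sided 0.05 margin test and becomes about 70% if 0.05 is read as two-sided. The trial is not short of power to show a difference from zero: that power is about 95% or more on either reading. The unassigned range is about 9 to 12.4 observed points, reached with a chance of about 15% under the planned effect and about 30% if the true reduction is 12 points.

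These figures assume 216 evaluable patients per arm, 40% events under the selective strategy, an absolute margin, normal approximations and no allowance for the interim look.

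**What to change.** 1. Name one risk-difference test or confidence interval for the primary endpoint that can address a margin, in place of Fisher's exact test.
2. State its sidedness in the analysis section so that it agrees with the power section.
3. Use a fixed sequence on the same interval: first, whether the reduction exceeds zero; then, only if it does, whether it exceeds 5 points. Because the hypotheses are nested, no alpha is spent. Say in advance which conclusion each step supports.
4. Label the log-rank test supportive.
5. State the null hypothesis and sidedness of the interim P below 0.001.
6. Restate power to match. With one-sided 0.05 kept: about 97% for zero difference and 80% for the margin. With two-sided 0.05 adopted: about 95% and about 70%.

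The cost is a change of wording before the data are unblinded, with no extra patients. If two-sided 0.05 is chosen, the stated power for the margin claim falls by about 10 percentage points; restoring 80% would need 548 evaluable patients instead of 432.

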### Statistical analysis plan

To compare baseline characteristics between routine and selective strategy groups as well as the routine strategy group and the registration group, all interval-scaled variables will be presented as mean ± standard deviation. Skewed interval-scaled data will be reported as median (interquartile range). Categorical variables will be presented as frequency and proportion (percentage). Chi-squared or Fisher’s exact test will be used for comparison of categorical variables between groups, whereas Mann-Whitney *U* test or unpaired Student’s *t* test will be used for interval-scaled variables as appropriate.

To compare the endpoints between routine and selective strategy groups, each analysis will be performed by “intention-to-treat” and “per protocol”. Proportional or Fisher’s exact test will be used for analysis of the proportion of primary, secondary, and other endpoints between routine and selective strategy groups as appropriate. For primary endpoint, significantly greater than 5 % reduction of MACE in the routine strategy group compared with the selective strategy group will be analyzed. By using the same statistical methods, subgroup analysis will include comparison of the proportion of endpoints in subgroups of these two randomized arms, such as patients with critical limb ischemia (Rutherford classification of at least 4), chronic kidney disease (at least stage 3), end-stage renal disease, old age, different genders, tobacco smoking, diabetes mellitus, hypertension, hyperlipidemia, metabolic syndrome, anemia, bedridden, hypoalbuminemia, elevated high-sensitivity C-reactive protein level, and so on. Kaplan-Meier analysis will be used to study patient survival and event-free status by using the log-rank test (Cox-Mantel) to ascertain differences between groups. If more than one endpoint occurs within the follow-up period for assessing event-free status, only the first event will be used in the analysis. Generalized estimating equation will be used to address whether and how the clustering by centers. Missing data will be treated with the multiple imputation method.

Although the main purpose of this study is not to compare the endpoints between the routine strategy group and the registration group or between randomized groups and the registration group, similar analyses as above will be performed to explore differences among patients in these groups. For all analyses, a *P* value of less than 0.05 is regarded as statistically significant. All statistical analyses are performed by using IBM SPSS Statistics 22.0 for Windows (IBM Corporation, Armonk, NY, USA), but the subgroup analysis is performed by using SAS software (Version 9.1.3; SAS Institute Inc., Cary, NC, USA).

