### Data collection and outcome measurement

The minimum follow-up period is 1 year and the maximum is 3 years. Clinical outcomes are obtained by chart review if the patient is still in the hospital and followed up by clinic visit at 30 days after indexed PTA if the patient has been discharged from the hospital and every 6 months thereafter. If participants miss indicated clinic visits, study assistants will call or directly contact the participants or subjects’ family.

The primary endpoint is the composite major adverse cardiac event (MACE) on long-term follow-up. Pre-specified secondary endpoints include the MACE between the screening and 30 days after PTA, and the composite major coronary event on long-term follow-up. Other endpoints include death from any cause, congestive heart failure requiring hospitalization, and any coronary revascularization. The MACE includes cardiovascular death, non-fatal myocardial infarction, non-fatal stroke, and target vessel revascularization (any unplanned coronary vessel revascularization). The composite major coronary event includes fatal or non-fatal myocardial infarction, recurrent angina pectoris, and target vessel revascularization (any unplanned coronary vessel revascularization). The diagnosis of myocardial infarction and stroke has been previously described in detail [6]. Clinical follow-up will be performed 30 days after PTA and every 6 months until the end of the 1-year follow-up for the last randomly assigned participant. The follow-up schedule is listed in Table 2. All outcome data should still be collected for participants who discontinue or deviate from intervention protocols. The clear definitions of each component of primary and pre-specified secondary endpoints are provided to all assessors, and training of assessors to enhance the quality of measurements is performed on site initiation visit.

**Table 2 Tab2:** Follow-up schedule

	V0	Cath	PCI	CABG	PTA	V1	V2	V3	V4	V5	V6	V7	V8
Time elapse from PTA					0	30 (±7)D	24 (±2)W	48 (±2)W	72 (±2)W	96 (±2)W	120 (±2)W	144 (±2)W	168 (±2)W
CRF	001	002	003	004	005	006	007	008	009	010	011	012	013
Markers/SNPs/miRNAs					X								
CBC	X												
BCS	X												
BW/BH	X												
BP/HR	X					X	X	X	X	X	X	X	X
History and PE	X					X	X	X	X	X	X	X	X

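### The 5-point margin on MACE is tested on crude proportions over 1 to 3 years of follow-up, so the margin, the 40% and 24%, and the power have no fixed time point

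*Protocol article*

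**What the plan says.** All references are to the protocol article.

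- **Endpoint** (Data collection and outcome measurement): "The primary endpoint is the composite major adverse cardiac event (MACE) on long-term follow-up". No time point is attached.
- **Follow-up** (same section): "The minimum follow-up period is 1 year and the maximum is 3 years". Visits continue "every 6 months until the end of the 1-year follow-up for the last randomly assigned participant", so close-out is common and a patient's follow-up depends on when he or she was enrolled.
- **Test** (Statistical analysis plan): a proportion test or Fisher's "exact test will be used for analysis of the proportion of primary, secondary, and other endpoints between routine and selective strategy groups". For the primary endpoint, "significantly greater than 5 % reduction of MACE in the routine strategy group compared with the selective strategy group will be analyzed".
- **Time-to-event analysis** (same section): "Kaplan-Meier analysis will be used to study patient survival and event-free status", with a log-rank test and first events only. Neither the margin nor a landmark time is linked to it.
- **Sample size** (Power estimation and sample size calculation): "estimated risk reduced from 40 % to 24"%, "with a one-sided alpha of 0.05, a power of 80 %, and a superior margin of 5"%, at least 432 patients, 450 after 4% dropout. The two risks carry no time point.

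**The concern.** An absolute risk difference grows or shrinks with the time over which it is measured. A margin of 5 points therefore states a hypothesis only once a time is given. Here the primary decision rests on the share of patients with MACE by close-out, and that share counts a patient watched for 1 year in the same way as one watched for 3.

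Two things are at stake. First, the quantity compared with the margin depends partly on how recruitment was spread over calendar time, which has nothing to do with the strategies. Second, the planned 80% power cannot be checked, because nobody can say when 40% and 24% should have been reached. The interim analysis has the same problem. It looks at the primary endpoint when half the patients have been randomised and have completed 6 months, which is yet another follow-up mix.

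**Working it through.** **1. Reproduce the plan's sample size.** Inputs from the sample-size section: risks 0.40 and 0.24, margin 0.05, one-sided alpha 0.05, power 80%. With unpooled variance,

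n per arm = [0.40×0.60 + 0.24×0.76] × (1.645 + 0.842)² / (0.16 − 0.05)² = 216 after rounding up.

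Total 432, and 432/0.96 = 450. The plan's figures are reproduced exactly. The formula treats MACE as a binary outcome at a single time.

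**2. Keep the treatment effect fixed and vary only the follow-up mix.** The documents give no hazard shape, recruitment shape or time for 40% and 24%, so these are assumptions. Take constant hazards and 40% versus 24% at 2 years:

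- selective: −ln(0.60)/2 = 0.2554 per year
- routine: −ln(0.76)/2 = 0.1372 per year
- hazard ratio 0.537

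Crude risk = ∫ (1 − e^(−λt)) f(t) dt over 1 to 3 years, where f is the density of follow-up time. Power = Φ((d − 0.05)/SE − 1.645), where d is the crude difference, SE = √[(p₁(1−p₁) + p₂(1−p₂))/216], and p₁ and p₂ are the arm risks.

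| Recruitment | f(t) | Mean follow-up (years) | Selective | Routine | Difference (points) | Power |
|---|---|---|---|---|---|---|
| Late-weighted | (3−t)/2 | 1.67 | 34.2% | 20.3% | 13.9 | 68% |
| Uniform | 1/2 | 2.00 | 39.3% | 23.8% | 15.6 | 78% |
| Early-weighted | (t−1)/2 | 2.33 | 44.5% | 27.2% | 17.2 | 85% |

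**3. Change the hazard shape.** With a decreasing hazard (Weibull shape 0.5, cumulative hazards −ln(0.60)×(t/2)^0.5 and −ln(0.76)×(t/2)^0.5), the late-weighted and early-weighted patterns give 14.9 and 16.6 points, and power of 74% and 83%.

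**4. Change the time to which 40% and 24% belong.** With constant hazards and the same three recruitment shapes:

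- reached at 1 year: 19.9 to 21.9 points, power 94% to 98%
- reached at 3 years: 10.4 to 13.4 points, power 42% to 65%

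The unstated time point matters more than the recruitment shape.

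**5. A smaller effect near the margin.** Keep the selective hazard at 0.2554 and take a hazard ratio of 0.80 (assumption), so the routine hazard is 0.2043.

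- at 1 year: 22.5% − 18.5% = 4.1 points (from unrounded risks)
- at 3 years: 53.5% − 45.8% = 7.7 points
- crude difference over the three recruitment shapes: 5.7 to 6.9 points

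The same effect is below the margin at one horizon and above it at another.

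**The case against.** **The comparison is randomised.** Both arms have the same expected follow-up distribution, so the crude difference is a fair average over the follow-up the trial happens to have. This stands. A reader might infer that the primary test is biased or invalid, and the documents do not support that for a null of zero difference. But this trial's null is 5 points, and an average over an unplanned follow-up mix does not say what 5 points means.

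**The 40% and 24% may be meant as averages over 1 to 3 years.** Under uniform recruitment and the 2-year assumption the result is 15.6 points and 78% power, close to the planned 16 and 80%. So the design is not badly underpowered on that reading. The text does not say this is the reading, and power still moves with recruitment.

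**Time-to-event methods are planned.** They are, but the log-rank test addresses zero difference, and the margin is assigned to the proportions.

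**Stronger readings that do not hold:**

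- That recruitment pace could cut power to one third. This needs every patient to be followed for only 1 year, which does not fit a 1-to-3-year range.
- That recruitment shape alone carries an effect across the margin. In step 5 all three shapes stay above 5 points. It is the choice of horizon that crosses it.
- That Kaplan-Meier estimates would inflate the difference judged against the margin by censoring non-cardiovascular deaths. The margin is not tested on those estimates, and the article does not say how such deaths are treated in them.
- That multiple imputation would fill in outcomes after close-out. The article names the method for missing data and says nothing of time after close-out.

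**Conclusion.** The point holds as a fault in how the primary comparison is defined. It is not a claim of bias. The protocol fixes a crude proportion as the basis for an absolute 5-point decision while leaving the time undefined in the endpoint, the margin and the sample-size risks. This is a stated rule, so it is not a detail that a condensed article has merely left out.

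Its size is moderate if 40% and 24% are 2-year risks: 13.9 to 17.2 points and 68% to 85% power under constant hazards, less under a decreasing hazard. It is larger if the intended time is unknown, as step 4 shows. Every figure after step 1 rests on assumed hazard shapes, recruitment shapes and calibration times. The dependence on follow-up does not rest on any one of those choices, because under each calibration tried the difference and the power moved with the follow-up mix.

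**What to change.** Before any comparison by arm, including the interim analysis:

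1. Name one fixed horizon and one time origin. The visit table counts from PTA, so if randomisation is the origin, say so and confirm that follow-up reaches the horizon from that point.
2. State that 40% and 24% refer to that horizon, and restate the power there.
3. Test the 5-point margin on the difference in cumulative incidence of first MACE at the horizon, with an estimator that handles censoring and treats non-cardiovascular death as a competing event (Aalen-Johansen, for example).
4. Keep the log-rank test over all follow-up as supportive.
5. State how the interim analysis uses this definition, since some patients will then have only 6 months of follow-up.

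The horizon should follow the expectation behind 40% and 24%, and convenience should not decide it. Twelve months keeps 80% power only if those are the 12-month risks. If they are 2-year risks, constant hazards give 1 − 0.60^0.5 = 22.5% and 1 − 0.76^0.5 = 12.8% at 12 months, a difference of 9.7 points and power of about 36%. The documents do not settle which applies. The historical 35% is reported at a median of 10 months, which is itself a rate over varying follow-up.

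Cost: a protocol amendment and a new power statement. The planned Kaplan-Meier analysis already needs event dates, so no new data are required. Events after the horizon would count only in the supportive analysis, and the stated power may change.

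### Subgroups are to be compared with the main two-arm test repeated inside each one at P<0.05, which does not test whether the effect differs between subgroups

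*Protocol article*

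**What the plan says.** All of this is in the protocol article, section Statistical analysis plan.

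- **Main comparison.** The arms are compared by a two-sample test of proportions or by Fisher's method: "exact test will be used for analysis of the proportion of primary, secondary, and other endpoints between routine and selective strategy groups as appropriate". The question on the primary endpoint is whether the reduction in MACE exceeds 5%.
- **Subgroups.** With the tests of the main comparison, "subgroup analysis will include comparison of the proportion of endpoints in subgroups of these two randomized arms".
- **Factors.** Critical limb ischemia comes first, then "chronic kidney disease (at least stage 3), end-stage renal disease, old age, different genders, tobacco smoking, diabetes mellitus, hypertension, hyperlipidemia, metabolic syndrome", then "anemia, bedridden, hypoalbuminemia, elevated high-sensitivity C-reactive protein level, and so on". That makes 14 named factors and an open end.
- **Threshold.** For all analyses, a P "value of less than 0.05 is regarded as statistically significant".

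The section also assigns the subgroup analysis its own software. Generalized estimating equations are mentioned only for clustering by centre. Exploratory language is used only for comparisons with the registration group, not for subgroups of the two randomized arms.

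**The concern.** The stated method repeats the routine-versus-selective test on smaller sets of patients. Each result answers a question about that set alone. Significance in patients with diabetes and non-significance in patients without it is not evidence that diabetes changes the effect. The second result may only reflect fewer patients or chance. The test that addresses effect modification compares the two stratum effects with each other, and the stated method does not do that.

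Two features add to this. One threshold of 0.05 applies to every test, and the open end of the list lets further subgroups join later. At stake is how the subgroup tables can be read. The trial concerns who should have coronary angiography before PTA, and a column of within-subgroup P values invites conclusions about who benefits that the tests cannot support. The primary analysis is not affected.

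**Working it through.** **Inputs from the protocol article (Power estimation and sample size calculation).** Event risks 40% (selective) and 24% (routine); one-sided alpha 0.05; power 80%; superiority margin 5%; 432 evaluable and 450 enrolled with 4% dropout. The Abstract gives 1:1 allocation. **Assumed:** subgroup prevalences, which the documents do not give.

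**1. The plan's own figure.** Variance term: 0.40×0.60 + 0.24×0.76 = 0.4224. Per arm: 0.4224 × (1.645 + 0.842)² / (0.16 − 0.05)² = 215.9, so 216. Total 432, and 432/0.96 = 450. The stated sample size reproduces. The plan gives no subgroup figure.

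**2. Same effect in everyone, both strata tested, 50:50 split.**
- Patients per arm per stratum: 216/2 = 108.
- SE of the risk difference: √(0.4224/108) = 0.0625.
- Power per stratum, two-sided 0.05: Φ(0.16/0.0625 − 1.96) = Φ(0.60) = 0.725.
- Exactly one stratum significant: 2 × 0.725 × 0.275 = 0.40.

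**3. Same, 30:70 split** (about 65 and 151 per arm).
- SEs: √(0.4224/65) = 0.081 and √(0.4224/151) = 0.053. Powers: about 0.51 and 0.86.
- Exactly one significant: 0.51×0.14 + 0.49×0.86 = 0.49.

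**4. Same as step 2, with the 5% margin and one-sided 0.05.** Power per stratum: Φ(0.11/0.0625 − 1.645) = Φ(0.115) = 0.546. Exactly one significant: 2 × 0.546 × 0.454 = 0.50. The margin does not remove the problem.

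**5. Simulation.** 2,000 trials per scenario; 225 per arm; 14 uncorrelated binary factors measured on the same patients; the same effect in every patient. Prevalences: all 0.5, all 0.3, or mixed from 0.15 to 0.8. Event risk under no effect: 40% or 32%.

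| Quantity, one endpoint | Result |
|---|---|
| Design effect: one stratum significant and the other not, per factor | 40–49% |
| No effect: at least one P<0.05, 14 tests | 35–45% |
| No effect: at least one P<0.05, 28 tests (both strata) | 48–52% |
| No effect, 5% margin test, 14 or 28 tests | 6–15% |
| At least one P<0.05 among 14 interaction tests | 51–54% |

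The last row is about the same with and without an overall effect. The gain from interaction tests is that they answer the right question, not that they control multiplicity.

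**The case against.** Several objections have force.

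- **Complementary strata.** Most factors are named only by the affected group; of the 14, only gender clearly names both strata. The 28-test count and the 40–49% figure need both strata to be tested, which the text does not say. This stands as a condition. Testing only the affected group still does not test effect modification.
- **The margin.** The sentence on the 5% margin comes just before the subgroup sentence, so the same methods may include it. The article does not settle this. If it does, the rate under no effect falls to 6–15% for MACE, but the margin is stated only for the primary endpoint.
- **Larger error rates.** A reader might infer 1 − 0.95¹⁴ = 51% or 1 − 0.95²⁸ = 76%. Those figures assume independent tests, no margin and, for the second, both strata tested. Subgroups drawn from the same patients do not give independent tests.
- **Certainty of false findings.** A reader might infer that the plan will produce false subgroup claims. The figures are probabilities, and the article nowhere says that a significant subgroup will be read as a different effect.
- **A condensed article.** An unseen analysis plan may add interaction tests, cut-offs or an exploratory label, and the text says that the subgroup analysis will include these comparisons, not that it is confined to them. So their absence is no finding. What stands is the positive choice: the article fixes the test, the factors and the threshold.

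**Conclusion.** The point holds as a criticism of a stated method. Within-subgroup tests at P<0.05 do not show whether the effect of routine angiography differs between patients.

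Its size rests on assumptions. If the design effect is uniform and both strata are tested, a misleading contrast arises in about 40% of factors at a 50:50 split and in 40–49% over the assumed prevalences. With no effect, at least one nominally significant subgroup for one endpoint has a chance of about 35–45% (14 tests) or 48–52% (28 tests), or about 6–15% for MACE under the margin test. The simulated figures treat the 14 factors as uncorrelated with each other. The article does not support the claim that false findings are certain, or that the sample size or primary comparison is at fault. This should be changed, but it does not threaten the main result.

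**What to change.** Replace the subgroup sentence so that it does four things.

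1. **Test the interaction.** For each listed factor, test treatment by subgroup on the risk-difference scale. The primary analysis is a proportion test, so there is no existing model to which a term can be added, and the test must be named. It can be (d₁ − d₂)/√(v₁ + v₂) from the stratum risk differences and their variances, or a binomial or GEE regression with an interaction term.
2. **Report estimates.** Give the risk difference and confidence interval in each stratum, with no within-stratum P values.
3. **Close the list.** Delete the open end. If the sponsor wants a short primary list, the sponsor should choose it.
4. **Handle multiplicity.** Label all subgroup results exploratory, or adjust across the listed factors; Bonferroni over 14 would be 0.05/14 = 0.0036. This is needed because interaction tests alone leave about a 51–54% chance of at least one false signal over 14 factors.

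**Cost.** Wording and a little programming; no change to data or sample size. The price is low power. At a 50:50 split the SE of the difference between strata is √2 × 0.0625 = 0.088. With 80% power at two-sided 0.05, the smallest detectable difference is (1.96 + 0.84) × 0.088 = 0.25, or about 25 percentage points. That exceeds the whole 16-point design effect, so a non-significant interaction should not be read as proof of a uniform effect.
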